#### Active arm (PCET)

##### Picture-based cue-exposure therapy (PCET)—weeks 1 to 3

The active control arm will consist of an intensive 3-week treatment of 15 sessions of PCET. The PCET phase will consist of a total of 60 repeated 10-min PCE to cocaine-related cues spread out on 15 PCET sessions. All meetings will last 90 min. PCET sessions will occur during 3 consecutive weeks period (weeks 1, 2, and 3) and delivered on 5 consecutive days—from Monday to Friday. As aforementioned and outlined for VRCET, PCET will be habituation-focused only.

PCET will be performed using laptop-displayed standard PowerPoint slides stemming from VRCE screenshots (Figs. 4, 5, 6, 7, and 8). Participants will be seated on a stool in front of the laptop and PCE will be non-interactive. PCE structure, situations, hierarchy, and switching rules from one PCE situation to another will be similar to the ones outlined for VRCET. See Table 1, Table 2, and Table 3 for detailed descriptions of VRCET, PCET, and MFCT.

**Table 2 Tab2:** Structure of CET sessions across VRCET and PCET interventions (experimental and active control arms)

**Welcoming participant** Active listening and problem solving on between-sessions cognitive-emotional difficulties; Resuming CET session plan and principles
**VRCE/PCE #1:** Situation 3 [10 min]
**Cocaine craving measures** During cue exposure (orally assessed): single-item (/10) Immediately after cue exposure (self-reported questionnaire): CEQ (S)
Wash-out procedure: resuming cue exposure course
**VRCE/PCE #2:** Situation 1 (10 min)
**Cocaine craving measures** During cue exposure (orally assessed): single-item (/10) Immediately after cue exposure (questionnaire): CEQ (S)
Wash-out procedure: resuming cue exposure course
**VRCE/PCE #3:** Situation 3 (10 min)
**Cocaine craving measures** During cue-exposure (orally assessed): single-item (/10) Immediately after cue exposure (questionnaire): CEQ (S)
Wash-out procedure: resuming cue-exposure course
**VRCE/PCE #4:** Situation 1 (10 min)
**Cocaine craving measures** During cue exposure (orally assessed): single-item (/10) Immediately after cue exposure (questionnaire): CEQ (S)
**Wash-out and safety procedure**: resuming cue-exposure course and session; paced-breathing relaxation; cocaine craving check
**End of CET session**

^*^During the next CET session, for cue exposure between/intra-session spacing and diversifying purposes, participants will be exposed to the ensuing situations order, according to their individualized exposures hierarchy: Situation 4, Situation 2, Situation 4, Situation 2

**Table 3 Tab3:** Number and content of MFCT sessions (experimental arm; [39])

	**Session content**
Session # 1	•Resuming MFCT plan
	•Psychoeducation about cocaine effects on brain
	•Advantages and disadvantages of quitting cocaine use
	•Functional analysis of recent using episodes (situational, cognitive and emotional triggers)
Session # 2	•Psychoeducation about memory reconsolidation
	•Functional analysis of recent cocaine use episodes (situational, cognitive and emotional triggers)
Session # 3	•Relieving of one significant cocaine use episode
	•Out of relieving-cognitive restructure
Session # 4	•Relieving of one significant cocaine use episode
	•In relieving-cognitive restructure
Session # 5	•Relieving of one significant cognitively-restructured cocaine use episode
	•Relapse prevention focused-skills training

### Criteria for discontinuing or modifying allocated interventions {11b}

Participants will be able to discontinue their participation any time during the protocol. The principal investigator will oversee documenting reasons of early cessations thoroughly. The principal investigator will be allowed to permanently end any participation in the study, for any reason putting at significant risk participant safety or compliance to the protocol. Criteria for discontinuation include:Long-term hospitalization (> 1 month) for other than CUDAbsence to 3 consecutive sessions

In case of discontinuation, the data collected will be analyzed and the participants will not be substituted.

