#### In and post-treatment measuring times (V1, V2, and V3)

The first measuring time (T1) will take place after 2 weeks of treatment, at the 11th treatment session and prior to start the MFCT (experimental arm) or second PCET (active control arm) phase. This will thus allow for comparing short-term research primary and secondary outcomes between VRCET and PCET, after 10 consecutive sessions of exposure.

The second measurement time (T2) will take place at the end of treatment (week 3), at the 15th and last treatment session. This will thus allow for comparing short-term research primary and secondary outcomes between VRCET + (10-session VRCET and 5-session MFCT) and PCET, after 15 consecutive sessions.

The third and last measuring time (T3) will consist in a follow-up visit taking place 1 month after the end of treatment (week 8). This will thus allow for comparing medium-term research primary and secondary outcomes between VRCET + (10-session VRCET and 5-session MFCT) and PCET, 1 month after 15 consecutive sessions of each therapeutic arm. Patients’ participation will end after this visit.

For each of these measurement times, subjective self-report questionnaires and objectives measures related to research objectives will be administered (Fig. 10).

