### Plans to promote participant retention and complete follow-up {18b}

Prior to each measurement time (T0, T1, T2, and T3), participants will be reminded of the therapeutic and scientific importance of dully completing each intervention and assessment phase. For the follow-up assessment, the investigators will contact the participants to collect study outcomes. A 20 € voucher will be offered to any outpatient participant in the follow-up assessment phase willing to use public transport for coming to their respective investigation center. Participants will be reminded that they may discontinue their consent to participate at any time during protocol, without justifying any reason and with no impact on their TAU. Data collected in participants who withdraw their consent will be analyzed.

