## Statistical methods

### Statistical methods for primary and secondary outcomes {20a}

Statistical analyses for principal and secondary outcome will be computed from self-report scales raw total scores or physiological signals (i.e., blood pressure, skin temperature and conductance) using, respectively, R Statistical [66] and OpenSignals (© PLUX S.A.) software. Our comprehensive data working R code, including R packages and inferential statistical hypothesis testing assumptions (Gaussian distribution, homoscedasticity, etc.), will be made available. For each primary or secondary variable of interest, descriptive statistics (n, min, max, median, q1, q3, iqr, mean, sd, se, and mean ci) will be computed using the *rstatix R* package. Primary inferential statistical analyses will consist of two-tailored independent *t*-tests on score changes between T0 (baseline) and T2 (post-treatment) in the experimental (i.e., VRCET +), compared with the active control therapeutic arm (PCET). In case of mostly non-normal variable distributions but symmetrical score differences around the median, Friedman and Bonferroni-corrected Wilcoxon signed-rank tests will be performed to test and contrast score differences between the conditions using *stats* and *rstatix R* packages [67]. In case of non-symmetrical paired score differences, Bonferroni-corrected Sign tests will be performed. Causal mediation analyses will be adjusted for confounding factors. Cohen’s d, Kendall’s W, and Cliff’s delta effect sizes for score changes across treatment arms (“negligible,” “small,” “medium,” and “large” effect for Cliff’s d inferior to 0.15, 0.33, 0.47, and superior to 0.47; [68]) with 95% CIs will be computed using *irr* and *effsize R* packages.

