### Methods in analysis to handle protocol non-adherence and any statistical methods to handle missing data {20c}

Given the small target sample size (*n* ≈ 50) and in case of arbitrary pattern of missing data, if applicable, multiple imputations for incomplete multivariate data will be performed on all missing data, using the *Amelia R* package [69, 70]. Our comprehensive imputation *R* code will be made available.

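### The discontinuation criteria do not separate stopping trial therapy from leaving the study, so patients removed for non-attendance may have no observed T2 or T3 outcome

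*Protocol article*

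**What the plan says.** Section {11b}, on discontinuing or modifying allocated interventions, gives the principal investigator a discretionary power to "permanently end any participation in the study". The grounds are a significant risk to the participant's safety or to compliance with the protocol. Two criteria for discontinuation follow: a hospitalisation of more than one month for something other than CUD, and absence from three sessions in a row. On the data, the section says: "In case of discontinuation, the data collected will be analyzed and the participants will not be substituted".

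Section {20a} makes the primary analysis an independent t-test on the change from T0 to T2. The section on measuring times fixes T2: "The second measurement time (T2) will take place at the end of treatment (week 3), at the 15th and last treatment session". T3 follows one month after the end of treatment, and of that visit it says: "Patients’ participation will end after this visit".

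Section {18b} adds: "For the follow-up assessment, the investigators will contact the participants to collect study outcomes". It offers a transport voucher for the follow-up assessment. Section {20c} plans multiple imputation for all missing data, introduced with the condition "in case of arbitrary pattern of missing data".

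**The concern.** Stopping therapy and leaving the study are different events. A patient who stops attending can still be asked to complete the outcome measures, and a comparison of the arms as randomised needs those measures. Section {11b} merges the two: the heading speaks of interventions, the power it grants concerns study participation, and the list of criteria does not say which of the two is discontinued.

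A site that follows the text literally may close a patient's participation after three absences and collect nothing more. Absence could reflect relapse, strong craving or dislike of one modality. The article does not say so, but it is a plausible inference. The arms differ in modality throughout and in content in week 3, so attendance could also differ between them. The primary outcome would then go unobserved in a group that need not resemble those who stay.

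**Working it through.** **1. Can the criterion remove the primary outcome?** Both arms have daily sessions from Monday to Friday, 15 in all, so three consecutive absences can occur within one week. T1 is taken at session 11, T2 at session 15 and T3 one month later.

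- Participation ended before session 11: only T0 is observed.
- Participation ended between T1 and session 15: T0 and T1 are observed, T2 and T3 are not.

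In both cases the T0 to T2 change is missing.

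**2. Does another section restore it?** Section {18b} promises contact for the follow-up assessment. It neither includes nor excludes patients whose participation was ended, and it does not concern T2. Section {11b} keeps the data collected but does not say that collection goes on. No section shown does.

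**3. What does imputation do?** Section {20c} covers all missing data, so these patients need not drop out of the analysis. Multiple imputation as usually applied assumes that, given the observed data, missingness does not depend on the unseen values. For a patient removed early, little beyond T0 is available to condition on. If the patient left because of craving or relapse after the last assessment, the imputed T2 value is likely to be too favourable.

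**4. Illustration of bias (all inputs assumed; the article gives none).** Let p_E and p_C be the proportions without T2 in the experimental and control arms, and k the gap in SD by which lost patients do worse than retained ones. Completers overstate an arm's mean by p × k, so

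bias in the difference = (p_E − p_C) × k.

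| p_E | p_C | k = 0.5 | k = 1.0 |
|---|---|---|---|
| 10% | 10% | 0 | 0 |
| 20% | 10% | 0.05 SD | 0.10 SD |
| 30% | 10% | 0.10 SD | 0.20 SD |
| 10% | 20% | −0.05 SD | −0.10 SD |

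A positive sign favours the experimental arm. These figures are for a completers' comparison. With imputation, k would be only the part of the gap that the observed data do not explain.

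**5. Illustration of precision.** The planned total of 54 (27 per arm) cannot be uniquely reproduced, because neither the numerical effect size nor the dropout rate is stated. A two-sided t-test at 0.05 with power 0.95 needs 54 for d = 1.0 before any dropout, 50 for d = 1.05 and 46 for d = 1.1. Power for loss from any cause, equal in both arms:

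| T2 values lost | d = 0.8 | d = 1.0 |
|---|---|---|
| none | 0.822 | 0.950 |
| 10% | 0.780 | 0.927 |
| 20% | 0.728 | 0.894 |

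This shows what missing T2 values cost in general. It does not measure the effect of this criterion, which is the loss with it minus the loss without it.

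**The case against.** Several stronger readings are tempting, and the article does not support them.

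- **That three absences remove a patient automatically.** The investigator is allowed to end participation, not required to. Loss of T2 and T3 is possible, not certain.
- **That the primary comparison becomes one of attenders.** Section {11b} keeps the data of discontinued patients in the analysis, and {20c} imputes all missing data. What stands is narrower: an imputed outcome is a weaker substitute for an observed one when loss depends on something unobserved.
- **That imputation is ruled out because drop-out is monotone while {20c} speaks of an arbitrary pattern.** The article does not exclude monotone loss, and a trial with many questionnaires and four time points will probably have mixed missingness.
- **That the power and bias figures measure this criterion.** They set assumed loss against no loss. A patient absent for three days running may have left the ward or be refusing contact, and might miss T2 whatever the wording. The sample size section also says that dropouts were allowed for, though without a rate.

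Two further objections carry weight. The article condenses a full protocol that is not shown and may provide for continued assessment; even then, the published sentence says that participation can end, and it should be reconciled. Secondly, the same power covers removals for safety, and the CEQ-S part of the primary outcome is taken after a VR exposure to cocaine cues. A blanket instruction to keep assessing everyone would therefore be too broad.

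**Conclusion.** The point holds in a limited form. Section {11b} does not distinguish stopping therapy from leaving the study. It allows study participation to be ended for non-compliance, lists three consecutive absences as a criterion, and is not complemented by any statement that assessments continue. Patients removed in this way before T2 would have no observed primary outcome, and the planned imputation would not correct loss that depends on unobserved craving or relapse.

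The size is unknown. The 0.05 to 0.20 SD range rests on assumed differential loss of 10 to 20 points, an assumed gap of 0.5 to 1 SD and a completers' comparison. The bias is zero if loss and gap are equal across arms, and it changes sign if the control arm loses more. That absent patients do worse is an inference, not something the article states. The change is worth making because it is specific and cheap and reduces a bias that cannot be repaired after the data are collected.

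**What to change.** In {11b}, separate the two events and state that:

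- the absence criterion ends trial therapy only;
- participants who meet it are still invited to whichever of T1, T2 and T3 remain, unless they withdraw consent or are removed for safety;
- they are analysed in the arm to which they were randomised.

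As T2 is tied to the last session, say also that for these participants it is offered at the corresponding calendar time. Leave the rule for when therapy stops unchanged; that is a clinical matter on which no view is taken here.

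The cost is a change of wording and some effort to contact absent patients. The assessments themselves are already planned. The existing travel voucher covers only the follow-up visit, so attendance at T1 or T2 by someone who has left the ward would need separate support if the sponsor wants to offer it.

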### Strategies to improve adherence to interventions {11c}

Standardized training and scripted therapy handbooks (available on request) will be provided to the facilitators to ensure therapy adherence and reliable delivery of the experimental and active control treatments, and to make further replication possible.

### Relevant concomitant care permitted or prohibited during the trial {11d}

Participants involved in concomitant treatment as usual (TAU) psychotherapeutic or pharmacologic treatments for CUD other than those provided in the inpatient setting will be maintained in the protocol, but their data will be excluded for comparability purposes.

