#### Randomization

Eligible patients will be randomized by the research psychiatrist or psychologist in charge of the inclusion visit, using the Research Electronic Data Capture (REDCap) secure web application, in the VRCET + (experimental) or PCET (active control) therapeutic arm.

After randomization, participants will be invited to complete baseline self-reported measures as well as to perform a craving induction task related to primary and secondary research objectives. This craving induction task will consist of three 7-min 30 exposures and will systematically start with one VRE to neutral cues, followed by one VRE and one PCE to a cocaine-related situation. The order of these two exposures to cocaine cues (i.e., VRE thus PCE or PCE thus VRE) will be randomly counterbalanced for controlling for potential cue-induced carry-over effect between one exposure to the other. The exposures’ order sequence generation for each participant will be generated by the research methodologist, using the Research Randomizer secure web application, and provided to the investigator within sealed opaque envelope for the inclusion visit.

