#### Experimental or active control therapy (3 weeks)

Participants included will start therapy (experimental or active control arm) within 1 week after the inclusion visit as follows:VRCET + (experimental arm): 2-week phase of 10 VRCET sessions, followed by a 1-week phase of 5 MFCT sessions. The VRCET phase will essentially consist of 40 VRE to a progressive hierarchy of 5 diversified cocaine-related situations. The MFCT phase will be in accordance to the “Memory Focused Cognitive Therapy for Cocaine Use Disorder” therapist guide (for request: [39]), and will consist of cognitive restructuring and memory reconsolidation procedures along with imagery exposure to arousing memories of cocaine use.PCET (active control arm): 3-week phase of 15 PCET sessions. The PCET phase will essentially consist of 60 VRE to a progressive hierarchy of 5 diversified cocaine-related situations.

Both VRCET + and PCET sessions will last 1 h 30 min and will be delivered in an intensive 1:1 intervention format, on a daily basis, from Monday to Friday. The facilitator of VRCET + and PCET may differ, but each patient will have only one facilitator.

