## Assignment of interventions: blinding

### Who will be blinded {17a}

Patients and researchers will not be blinded after assignment to interventions given significant delivery modalities between VR-based and picture-based exposure therapies. Only the data manager in charge of the allocation sequence will be blinded to the assignment.

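### Data of randomised patients who have CUD treatment from outside the inpatient setting are to be excluded: an open-ended post-randomisation exclusion that can bias the arm comparison and always shrinks the sample

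*Protocol article*

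**What the plan says.** Item 11d (concomitant care) covers participants who have "psychotherapeutic or pharmacologic treatments for CUD other than those provided in the inpatient setting". They "will be maintained in the protocol, but their data will be excluded for comparability purposes". The item names no visit, no time window and no sensitivity analysis, and does not say whether the excluded values are dropped or imputed.

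The rest of the protocol article gives the context:

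- **Eligibility (item 10).** Outside CUD treatment is not among the non-inclusion criteria.
- **Randomisation.** "Eligible patients will be randomized by the research psychiatrist or psychologist in charge of the inclusion visit", and participants "will start therapy (experimental or active control arm) within 1 week after the inclusion visit".
- **Blinding (item 17a).** "Patients and researchers will not be blinded after assignment to interventions".
- **Discontinuation (item 11b).** "In case of discontinuation, the data collected will be analyzed and the participants will not be substituted". Item 18b likewise analyses data already collected from participants who withdraw consent.
- **Follow-up (item 18b).** A travel voucher is offered to "any outpatient participant in the follow-up assessment phase", so some participants are expected to have left hospital by T3. Participation ends after that visit.
- **Primary analysis (item 20a).** Independent t-tests on change from T0 to T2.

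**The concern.** Comparability of the arms comes from randomisation. A rule that deletes the data of randomised patients can remove that comparability, although comparability is the reason given for the rule. Patients with persistent craving, which is the primary outcome, may be more likely to seek further help. In an open-label trial, both taking outside care and classifying it as such can depend on the arm. If exclusion depends on arm and on outcome, the patients left in the two arms no longer have the same expected outcome, even when the treatments are equivalent.

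The rule also discards data that the trial will already hold, because these patients stay in the protocol. The sample size section allows for dropouts and does not mention retained patients whose data are set aside.

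**Working it through.** **Which patients the rule removes.** Outside care is not screened out at entry and randomisation takes place at the inclusion visit. Whether such care was under way at entry or began later, the data are removed after randomisation.

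**Inputs.** From the protocol: 54 randomised 1:1, so 27 per arm; two-sided alpha 0.05; power 0.95. Not in the protocol, hence assumed: the share excluded in each arm and the correlation r between the tendency to have outside care and a poor outcome. The effect size is described only as large and no dropout rate is given, so 54 can be neither confirmed nor refuted. A two-sample t-test needs 54 in total at d = 1.0 with no dropout, and 84 at d = 0.8.

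**Bias with no true effect.** Let the outcome be standard normal with higher scores worse. In each arm, exclude the share p with the highest value of a normal latent variable that correlates r with the outcome. The mean of those who remain is −r × φ(z)/(1 − p), where z is the (1 − p) quantile and φ the normal density.

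- p = 0.05: 0.1031/0.95 = 0.109
- p = 0.20: 0.2800/0.80 = 0.350
- Difference: 0.350 − 0.109 = 0.241
- Bias at r = 0.7: 0.7 × 0.241 = 0.17 SD
- Bias at r = 0.3: 0.3 × 0.241 = 0.07 SD

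**Type I error.** By simulation under the same model, with a t-test on those who remain:

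| Excluded (control vs experimental) | r | Bias (SD) | Type I error | Mean N analysed |
|---|---|---|---|---|
| 20% vs 5% | 0.7 | 0.17 | about 9% | 47 |
| 20% vs 5% | 0.3 | 0.07 | about 6% | 47 |
| 30% vs 10% | 0.5 | 0.15 | about 8% | 43 |
| 30% vs 10% | 0 | 0.00 | about 5% | 43 |
| 20% vs 20% | 0.7 | 0.00 | about 5% | 43 |

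Mean N is 27 × (1 − p) summed over the arms. For 20% vs 5% it is 21.6 + 25.65 = 47.25, and for 20% in both arms 2 × 21.6 = 43.2.

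**Direction.** When more controls with poor outcomes are removed, the remaining controls look better than they should. In the first row nearly all false rejections then favour control, and about 0.5% favour the experimental arm. If the imbalance is reversed, nearly all favour the experimental arm.

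**Power.** With 0%, 20% and 30% excluded overall, N is 54, about 43 and about 38. Power is then 0.95, 0.89 and 0.85 at d = 1.0, and 0.82, 0.73 and 0.67 at d = 0.8.

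**The case against.** The strongest objection concerns the primary endpoint. Change from T0 to T2 is measured in hospitalised patients over three weeks of daily sessions, and care given in the inpatient setting is exempt. Few may have outside CUD treatment in that period. This stands: the primary effect may be small. However, the rule has no visit limit, so on one reading care begun after T2 could also remove a patient's T2 data.

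Four stronger readings are tempting, and the documents do not support them.

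- **That outside care necessarily begins after randomisation.** The wording could also cover care already under way at entry. Excluding on such a pre-existing characteristic would cost power but would not by itself produce the arm-dependent bias shown above.
- **That most of the T3 data would be lost.** Item 18b shows only that some participants may be outpatients by then. It gives no share and does not say that they will be in CUD treatment.
- **That items 11d and 11b contradict each other.** Item 11b covers patients who discontinue and item 11d patients who stay but have other treatment, so both can be applied. They do follow different principles: data from those who leave are analysed, while data from some who stay are discarded. A patient who discontinues and also has outside care falls under both.
- **That the rule favours the experimental arm.** The direction depends on which arm loses more patients with poor outcomes. If that is the control arm, the bias works against the superiority hypothesis.

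It is also fair to say that the simulated rates and correlations are chosen, not observed. With equal exclusion, or exclusion unrelated to outcome, there is no bias.

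**Conclusion.** The point holds as a fault in a stated analysis rule. Item 11d is not a detail left to an analysis plan, and nothing elsewhere in the protocol article overrides it. Followed as written, it can bias every between-arm comparison, and any exclusion reduces the number analysed beyond the dropouts allowed for.

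The size is illustrative. Bias of 0.07 to 0.17 SD and type I error of about 6% to 9% follow from assumed exclusion of 20% versus 5% and correlations of 0.3 to 0.7. Under equal exclusion only the loss of sample remains. Confidence is high that the rule should not define the primary analysis set. It is lower that the T2 result would be materially biased, because the share affected is not stated and may be small while patients are in hospital. The exposure is plausibly greater at T3.

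**What to change.** In item 11d, delete the clause that excludes these participants' data. State that the primary analysis includes all randomised patients in their allocated arm with all collected data. Record CUD treatment from outside the inpatient setting by type and date, and report it by arm. Keep the exclusion, if wanted, only as a labelled sensitivity analysis, with the visits and time window that trigger it defined. Align the wording with items 11b and 18b, and say in item 20c how values set aside in the sensitivity analysis are handled.

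The cost is a short protocol change, best made before analysis. No new visits are needed, because these patients already stay in the protocol. The downside is some dilution of the contrast by co-treatment, which reporting by arm makes visible. Which concomitant care is permitted is a clinical matter and is not judged here.
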